#### Data analysis plan

We will use a modified intention-to-treat population approach and include participants with valid baseline data and at least one post-baseline data point. Missing data among these participants will be handled using multiple imputations, clearly described, and with sensitivity analysis to test the robustness of the results.

Primary outcome analysis will be completed using a Fisher’s exact test to compare the proportions of progression in the intervention and treatment groups. To analyze secondary and exploratory outcomes between groups, we will use mixed-effects regression models to evaluate change in outcome as a function of group, time, and group-by-time interaction. We will also conduct longitudinal analysis within groups using repeated measures ANOVA to compare measures at time points, with covariates as fixed effects. Effect sizes and confidence intervals will be reported. Additionally, we will assess baseline sample characteristics and test for any baseline group differences using two-sample t-tests for continuous variables and Chi-square tests for categorical variables. We will also conduct an adherence analysis by reporting intervention session attendance rate and summary statistics for self-reported engagement with intervention domains and testing for any differences in these adherence metrics based on cohort number, age/sex, and other covariates. We will conduct sensitivity analyses aligned with best practices to see if the outcome analysis results are robust to any potential confounders, including baseline imbalance or intervention non-compliance.

For further exploratory analyses of relationships of multi-omic biomarkers with MLI, we will assess proteomic, metabolomic, and microbiomic biomarkers from our selected panels for detectable change over the course of the study, using a linear mixed-effects model, controlling for age, sex, and education, to determine whether biomarker concentrations change over time (baseline to 3 months and 12 months). For the biomarkers with significant time coefficient, we will re-run the model, adding a lifestyle score based on self-reported engagement with the intervention domains, to test for a role of lifestyle in the change over time. Additionally, we will test for simple associations between lifestyle and biomarkers by calculating Spearman correlations of each biomarker with self-reported engagement with each intervention domain, as well as with a composite total at baseline, 3 months, and 12 months. Finally, we will complete integrative multi-omic analysis that tests for covariance in changes in biomarkers over time.

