### Arms and interventions

Two hundred participants will be randomized equally to two study arms (*n* = 100 each): the intervention arm and the control observational arm. The sequence of group allocation was generated by the study data scientist using computer-generated random numbers and uploaded to the secure study REDCap database, where it can be administered by the study team. Each participant’s start date is based on participant availability, and, once enough participants (at least five) are identified that can meet at the same time, an intervention group and matching control group of comparable size will begin study activities on the same schedule. The experts completing quality assurance of the testing and analysis of the multi-omic data, including imaging, electrophysiology, and patient reported outcome measures are blinded to group allocation.

The intervention group will receive synchronous, virtual 2-hour weekly intervention sessions for 12 weeks. The control group will receive the standard of care during this time. Both groups will receive a MINDS study activity survey (see Supplemental Material 1) every 2 weeks during the first 12 weeks, followed by every month until the end of the 12-month study period. Each two-hour intervention session includes check-in and discussion of homework, followed by two 50-minute sessions, split evenly between two of the four intervention domains, with rotation through the domains and topics each week so that participants receive an even dose of intervention domain. See Supplemental Material 2 for an overview of the 12-week intervention sessions.

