#### Sample size calculation

Our enrollment goal is 200 participants randomized to each group (intervention and control). Based on an attrition rate of 10%, we estimate we will have 180 participants with data for analysis. For primary outcomes analysis of binary outcomes (i.e., progression/no progression), the detection of a standard large effect size (odds ratio = 4.27, converted from Cohen’s *d* = 0.8) of the intervention at 0.8 power with a two-sided alpha of 0.05 would require 18% of the control group attaining progression. For secondary outcomes between group mixed-effects regression analysis, we will be able to detect a medium effect size (Cohen’s *f* = 0.27) at 0.8 power and a 5% significance level.

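### The between-arm mixed model for continuous secondary and exploratory outcomes is valid, but it leaves out baseline adjustment and so gives up precision that would cost nothing

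*Protocol article*

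**What the plan says.** In the protocol article, the Data analysis plan gives the between-group analysis of secondary and exploratory outcomes as "mixed-effects regression models to evaluate change in outcome as a function of group, time, and group-by-time interaction". No other term is listed. It does not say whether the response is the raw score or the change from baseline, or which contrast carries the treatment effect.

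Three other statements bear on this:

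- The analysis set will "include participants with valid baseline data and at least one post-baseline data point", so a baseline value exists for everyone analysed.
- Covariates do appear elsewhere in the section. The within-group repeated measures ANOVA has unnamed covariates as fixed effects, and the further exploratory biomarker model is fitted "controlling for age, sex, and education". Baseline imbalance is left to sensitivity analyses.
- The biomarker model describes change over time as "baseline to 3 months and 12 months". Table 1 schedules the questionnaires at the same three times.

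The Sample size calculation section gives the detectable effect for the secondary mixed-effects analysis as Cohen's f = 0.27 "at 0.8 power and a 5% significance level". The Perspective section concedes that the primary outcome may see too little progression in 12 months, and points to the secondary outcomes as a more sensitive support.

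**The concern.** Randomised arms have the same expected baseline mean. A model with free group, time and group-by-time terms, and baseline among the visits, estimates a separate baseline mean for each arm. The group-by-time contrast then subtracts the full observed baseline difference, as a change score does, although that difference is chance. Baseline adjustment subtracts only the part that predicts follow-up, and for any correlation below 1 it has the smaller variance.

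What is at stake is precision on the questionnaire and biomarker outcomes, not validity. The protocol itself leans on these outcomes because the primary comparison may be underpowered, so a free gain in precision is worth having.

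**Working it through.** **Inputs.** "Two hundred participants will be randomized equally to two study arms" (Arms and interventions), and "Based on an attrition rate of 10%, we estimate we will have 180 participants with data for analysis" (Sample size calculation). Hence 180/2 = 90 analysed per arm. Two-sided α = 0.05 and power 0.80, so the multiplier is 1.960 + 0.842 = 2.802. The protocol gives no baseline-to-follow-up correlation, so ρ is assumed from 0.3 to 0.9. The outcome SD is taken as equal at baseline and follow-up and set to 1.

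**The plan's own figure.** With a noncentral F and λ = N f², a one-way layout of 6 cells (2 groups × 3 times, numerator df 5) and N = 180 gives a detectable f of 0.271, with power 0.796 at f = 0.27. That reproduces the stated value, although the layout is inferred and not stated. A two-group contrast with N = 180 would detect f = 0.210. For two equal groups d = 2f, so f = 0.27 corresponds to d = 0.54.

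**Variance of the between-arm contrast at one follow-up visit** (per-participant factor):

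- Change score, i.e. group-by-time with a free baseline: 2(1−ρ)
- Baseline-adjusted or baseline-constrained: 1−ρ²
- Ratio: (1−ρ²) / [2(1−ρ)] = (1+ρ)/2

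**Detectable difference** = 2.802 × √(2 × factor / 90). At ρ = 0.5:

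- Change score: 2.802 × √(2 × 1.00/90) = 2.802 × 0.149 = 0.418 SD
- Adjusted: 2.802 × √(2 × 0.75/90) = 2.802 × 0.129 = 0.362 SD

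| ρ (assumed) | Change factor | Adjusted factor | Ratio | Detectable, change | Detectable, adjusted | Adjusted power for an effect with 80% power under change |
|---|---|---|---|---|---|---|
| 0.3 | 1.40 | 0.91 | 0.65 | 0.494 | 0.398 | 93.5% |
| 0.5 | 1.00 | 0.75 | 0.75 | 0.418 | 0.362 | 89.9% |
| 0.7 | 0.60 | 0.51 | 0.85 | 0.323 | 0.298 | 86.0% |
| 0.8 | 0.40 | 0.36 | 0.90 | 0.264 | 0.251 | 84.0% |
| 0.9 | 0.20 | 0.19 | 0.95 | 0.187 | 0.182 | 82.0% |

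In participants, the change-score analysis needs 1/0.75 = 1.33 times as many as the adjusted one at ρ = 0.5, and 1/0.85 = 1.18 times as many at ρ = 0.7.

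**Check with the longitudinal model.** Generalised least squares with three visits and compound symmetry gives standard errors for the month-12 contrast of 0.176, 0.149, 0.115 and 0.094 SD at ρ = 0.3, 0.5, 0.7 and 0.8 with a free baseline. With equal baseline means they are 0.142, 0.129, 0.106 and 0.089. These agree with the formulas.

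**Against the stated target.** At d = 0.54 the change-score contrast has power 0.865, 0.952 and 0.997 at ρ = 0.3, 0.5 and 0.7. The adjusted contrast has 0.967, 0.987 and 0.999. Both exceed 0.80.

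**Which term carries the effect.** Take a benefit δ that is equal at months 3 and 12.

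- Raw scores with baseline as a visit: group-by-time carries δ. The group main effect averaged over three visits is (0 + δ + δ)/3 = 2δ/3.
- Change scores at months 3 and 12 as the response: group-by-time has expectation δ − δ = 0 and rejects about 5% of the time. The group term carries δ.

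**The case against.** The strongest reply is that this is a one-clause summary in a journal article, and that the response, covariates and contrast are commonly left to an analysis plan that is not shown. That has force for the tested contrast and for the full covariate list, and neither is held against the protocol here. It has less force for baseline. The article lists the terms of the between-arm model, names covariates for other models in the same section, and places baseline imbalance among the sensitivity analyses. The main between-arm model as written is therefore unadjusted.

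A second reply is that baseline is used already, as a modelled visit, and that the test is unbiased. This is right, and it is why the point concerns efficiency alone.

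A third is that the gain depends on an unknown ρ and is small when ρ is high. This also stands: at ρ = 0.9 the variance falls by only 5%. It is never negative under the stated assumptions.

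A reader might go further and infer that the plan tests the wrong term, so that a sustained benefit would be detected no more often than chance. The documents do not support this. It requires that change scores at months 3 and 12 be the response and that the interaction be the test of benefit, and the protocol states neither. The inclusion rule and the visit schedule fit better with baseline as one of the modelled visits, where group-by-time is a valid test.

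A reader might also infer that covariates and baseline imbalance are ignored outside the biomarker models. The within-group ANOVA covariates and the planned sensitivity analyses show otherwise.

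**Conclusion.** The point holds as a loss of efficiency. The between-arm model as written is valid, but its variance is higher than it needs to be: baseline adjustment would remove 35% of it at ρ = 0.3, 25% at 0.5, 15% at 0.7 and 5% at 0.9. These figures rest on an assumed ρ, equal SDs at baseline and follow-up, and 90 analysed per arm.

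The protocol's stated target for secondary outcomes is safe at the correlations checked. The benefit is for effects smaller than that target. It is still worth taking, because the protocol counts on these outcomes if the primary comparison proves uninformative.

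The scope is limited to continuous questionnaire and biomarker outcomes. The argument does not reach the appearance of inclusion criteria for another disorder, which is a binary event, or the Fisher test of the primary outcome.

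**What to change.** For continuous questionnaire and biomarker outcomes, fit the mixed model to raw scores at baseline, month 3 and month 12, with the baseline mean constrained to be equal across arms. Equivalently, model months 3 and 12 with the baseline value as a covariate whose slope may differ by visit. State that the treatment effect is the between-arm difference at each follow-up visit in that model. This also removes any doubt about whether raw or change scores are meant, and with it the conditional risk that an interaction test would miss a sustained benefit.

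Leave the binary secondary outcome and the primary analysis as they are.

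The cost is a change of wording, best made before the arms are compared. No new data are needed, since a valid baseline is already a condition of entering the analysis.

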#### Exclusion criteria

Participants with impaired ability to participate in the study’s interventions will be excluded. Participants actively engaged in two or more of the study intervention domains are not eligible for participation. Participants scoring below an 8th grade English reading level on the WRAT-IV Reading subset are also excluded. Finally, participants who require a legally authorized representative (LAR) or are not able to consent for themselves are not eligible for participation.

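### The exploratory lifestyle–biomarker correlations are unadjusted, although the plan controls the same biomarkers for age, sex and education, so shared dependence on age can pass for a lifestyle association (minor)

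*Protocol article*

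**What the plan says.** All of this is in the protocol article, mostly under Data analysis plan.

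- The last paragraph of that section opens with "For further exploratory analyses of relationships of multi-omic biomarkers with MLI", so the status of the work is declared.
- Its first step assesses the biomarkers "using a linear mixed-effects model, controlling for age, sex, and education, to determine whether biomarker concentrations change over time".
- Its second step is conditional: "For the biomarkers with significant time coefficient, we will re-run the model, adding a lifestyle score based on self-reported engagement".
- Its third step is to "test for simple associations between lifestyle and biomarkers by calculating Spearman correlations of each biomarker with self-reported engagement with each intervention domain". A summed score over the domains is treated in the same way, and the correlations are repeated at each of the three sampling visits. No covariates are named here.
- The preceding paragraph plans an adherence analysis in which attendance and self-reported engagement are tested for differences by cohort, age, sex and other covariates. It also promises sensitivity analyses for confounding of the outcome results, but does not link these to the correlations.
- Study description and study design sets a lower age limit of 50 and gives no upper limit. Sample size calculation expects 180 participants with data.

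**The concern.** The plan treats both legs of a confounding path as plausible. It adjusts biomarkers for age, and it intends to look for age differences in engagement. It then correlates the two without adjustment, across all ages and all four risk groups.

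This matters because of the gate in the second step. A marker whose level does not change significantly over time never enters the adjusted model with a lifestyle score, so its only stated link to self-reported lifestyle is the raw correlation. One aim of the trial is to find biomarkers that predict whether the intervention works. A list of lifestyle-associated markers that owes part of its content to age would be a poor starting point for that aim.

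**Working it through.** **Inputs from the document.** The total randomised is 200 (Arms and interventions) and attrition is 10% (Sample size calculation). 200 × (1 − 0.10) = 180, which reproduces the plan's analysable number. The plan gives no figure of its own for the correlations.

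**Assumed inputs.** The document gives neither the age–marker correlation (a) nor the age–engagement correlation (b), so both are varied. A two-sided 5% level is also assumed; the plan sets it for the primary outcome, not for these correlations. Marker and engagement are taken to be unrelated once age is known, and all variables to be normal. Only age is modelled, not sex or education.

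**Step 1: the spurious correlation.** If age is the only link, the product-moment correlation between marker and engagement is a × b. The matching Spearman value is ρ = (6/π) × asin(ab/2).

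**Step 2: how often it is declared significant.** Use Fisher's z with variance 1.06/(n − 3). The multiplier is √(177/1.06) = 12.92, and |ρ| above tanh(1.96/12.92) ≈ 0.15 is nominally significant. The rejection rate is Φ(z − 1.96) + Φ(−z − 1.96), with z = 12.92 × atanh(ρ).

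Worked case, a = 0.5 and b = 0.2:
- ab = 0.10
- ρ = (6/π) × asin(0.05) = 0.0955
- z = 12.92 × 0.0958 = 1.24
- rejection rate = Φ(−0.72) + Φ(−3.20) ≈ 0.24

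**Step 3: check by simulation.** For each pair, 4,000 data sets of 180 were generated with no lifestyle effect. Each was tested with the plain Spearman correlation and with the rank-partial correlation given age.

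| a (age–marker) | b (age–engagement) | Formula, plain | Simulated, plain | Simulated, partial |
|---|---|---|---|---|
| 0 | 0 | 5% | 4% | 4% |
| 0.3 | 0.1 | 7% | 7% | 5% |
| 0.3 | 0.2 | 11% | 12% | 5% |
| 0.5 | 0.2 | 24% | 26% | 5% |
| 0.5 | 0.3 | 46% | 48% | 5% (4.5%) |
| 0.6 | 0.3 | 61% | 64% | 5% |

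The two routes agree to within about 2 percentage points. At the low end the problem disappears: by the formula, (0.2, 0.1) gives 6% and (0.1, 0.1) gives 5%.

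**The case against.** The best defence is that nothing here is misstated. The text calls these simple associations within exploratory work. A Spearman coefficient estimates a marginal association, and if age drives both variables that marginal association is real. It is a false positive only when read as evidence about lifestyle. An adjusted model beside a simple correlation is not a contradiction, and the randomised test of the exploratory outcomes is the group-by-time mixed model, which is untouched. This stands, and it keeps the point minor. It does not remove the point, because the stated purpose of the paragraph is the relationship between biomarkers and the intervention, and many markers may have no other test against reported lifestyle.

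It is also fair that the correlations with age are assumed, and that after allocation engagement should depend partly on randomised arm. Arm is independent of age in expectation, so the age–engagement correlation at 3 and 12 months is probably weaker than at baseline. Baseline has no such protection.

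A reader might infer several stronger criticisms that the document does not support:

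- **Survey noise hides real associations.** No reliability figure is given. The text does not say whether an engagement value is one survey or an average of those collected "every 2 weeks during the first 12 weeks, followed by every month until the end of the 12-month study period". Noise would affect the adjusted model as well, and covariates would not cure it.
- **No survey at month 3.** Table 1 leaves that cell blank, but the biweekly surveys run through the first 12 weeks, so one falls at or near that time.
- **The baseline composite has almost no range.** The rule is "Participants actively engaged in two or more of the study intervention domains are not eligible for participation". It sets no threshold for being active and does not imply zero scores on the other domains.
- **Change scores should replace visit values.** That answers a different question, and change is already analysed by the mixed model.
- **Multiplicity is uncontrolled.** That is a separate matter, commonly left to an analysis plan that is not shown.

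**Conclusion.** The point holds in a limited form. The correlations are specified without covariates that the same paragraph considers necessary for the same markers. For markers without a significant time coefficient they are the only stated test against self-reported lifestyle. Age can therefore produce apparent lifestyle associations.

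How often it would do so cannot be fixed from the document. Under the assumed age correlations, with 180 participants, the rejection rate runs from about 7% to 61–64% instead of 5%. It is 5–6% when the age correlations are small, and randomisation probably lowers it after baseline. These rates should be read as what could happen, not as a forecast. Severity is low: the analysis is exploratory, and the primary and secondary randomised comparisons are unaffected.

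**What to change.** Compute partial Spearman correlations (equivalently, rank regressions) adjusted for age, sex and education, which are the covariates the plan already uses. Base any statement about a lifestyle–biomarker association on these, and report the raw correlations as descriptive only.

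The cost is a few lines of code on covariates the plan already uses in its biomarker model. There may be fewer nominally significant exploratory results. No new data collection and no change to sample size or to the other analyses is needed.

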### Eligibility criteria

CCBS participants with increased risk of developing ADRD, PD, stroke, or epilepsy are eligible for the MINDS study. Risk factors for development of these disorders are based on the current available evidence (Table 2). These factors are not diagnostic for ADRD, PD, stroke, or epilepsy. The four neurological disorders show significant clinicopathological overlap, and a MINDS-eligible participant enrolled for stroke risk factors may develop dementia before a clinical stroke, or a participant enrolled due to risk of a neurodegenerative disorder may later develop seizures before the clinical manifestation of dementia. Study enrollment began in July 2023 and is expected to finish in December 2024.

### Risk factor inclusion criteria

#### Parkinson’s disease

Most patients diagnosed with PD show hyposmia that predates diagnosis by years. We define hyposmia as a score at or below the 10th percentile based on age and sex on the University of Pennsylvania Smell Identification Test (UPSIT). We used the 10th percentile as the hyposmia cut-off to increase the specificity and yield for progression to PD.

#### Alzheimer’s disease and related dementias

Participants qualify as at-risk for dementia development with a combination of low semantic memory scores and poor subjective memory assessment, which show during the prodromal phase as early as two decades before clinical onset. Differences in amyloid-beta biomarkers and semantic memory tasks are early indicators of diagnosis. We will use semantic memory for inclusion of at-risk participants performing 1.5 or more standard deviations below the healthy population mean on the Rey Auditory Verbal Learning Test (RAVLT). To enrich the study population with high-risk individuals, we will assess subjective memory via the Brief Assessment of Cognitive Health (BACH), with a score ≤ 40 qualifying participants for inclusion.

